### Primary outcome

#### Fatigue severity

Fatigue severity will be self-assessed using the Functional Assessment for Chronic Illness Therapy-Fatigue (FACIT-F) subscale at baseline and on day 5. FACIT-F is a well-validated quality-of-life instrument widely used for the assessment of CRF in clinical trials. It consists of 27 general quality-of-life questions divided into four domains (physical, social, emotional, and functional) and the 13-item FACIT-F fatigue subscale [33]. FACIT-F allows patients to rate the intensity of their fatigue and its related symptoms on a scale of 0 to 4 (0, not at all; 4, very much). The total score for FACIT-F is the sum of the four domains (physical, social, emotional, and functional) plus the fatigue subscale.

### Secondary outcomes

CRF most commonly occurs with other symptoms, such as depression, anxiety, pain, sleep disorder, and loss of functional status [7]. CRF profoundly impacts on a person’s physical, emotional, and mental well-being [11]. The secondary outcomes are listed below.

#### Symptom distress scores

Symptom distress scores will be self-assessed using the ESAS [34] at baseline and on day 5. This validation instrument will assess nine symptoms commonly experienced by cancer patients during the previous 24 h: pain, fatigue, nausea, depression, anxiety, drowsiness, dyspnea, anorexia, and well-being [35, 36]. These tools have been validated and are reliable for assessing the intensity of symptoms in patients with cancer [33, 34, 37].

#### Depression status

Depression and anxiety will be self-administered by the Hospital Anxiety and Depression Scale (HADS) at baseline and on day 5. This scale has been shown to be a valid and reliable measure of the severity of emotional disorders and is used in general hospital practice. Participants will be instructed to choose one response from a list of pre-provided answers that best describe their current feelings. The HADS is a 14-item self-report screening scale originally developed to indicate the presence of anxiety and depressive states in the setting of a medical outpatient clinic and is widely used to assess patients with advanced disease [38].

#### Sleep disorders

Sleep disorders will be self-administered using the Pittsburg Sleep Quality Index (PSQI) at baseline and on day 5. This questionnaire has been used as an effective instrument for measuring the quality and patterns of sleep. Several studies using the PSQI have confirmed its high level of validity and reliability [39].

#### Quality of life

Quality of life will be self-administered using the Functional Assessment of Cancer Therapy-lung (FACT-L) questionnaire. The FACT-L questionnaire measures 44 items rated on five subscales. This questionnaire has been used previously to measure QOL in the last 7 days for lung cancer patients, with each subscale using a 0 to 4 Likert scale. The four subscales (emotional, functional, physical, and social) query patient’s well-being. The fifth subscale queries the patient’s pulmonary (lung) functionality [40].

#### Levels of immunologic indicators

Blood samples will be collected at baseline and day 5 (the end of intervention) to measure the levels of immunologic indicators. T lymphocyte subgroups, natural killer cells, and TNF-α will be analyzed in the GPHCM laboratory. These are associated with postchemotherapy fatigue in patients [17].

### Safety

An independent Data and Safety Monitoring Committee will evaluate the progress of the study and assess the safety data, as requested during the study. Adverse events (AEs) will be defined as any undesirable experience participants endure during the trial period, regardless of whether or not it is associated with the intervention. Participants will be instructed to report AEs to the research team, and a research nurse will monitor participants for potential occurrences of AEs. All details of AEs, such as time of occurrence, severity, management, and causality to the intervention, will be recorded on case report forms. All AEs will be followed up from the date they are brought to the investigator’s attention until resolution. Severe AEs must be reported to both the GPHCM Data and Safety Monitoring Committee and the GPHCM Ethics Committee within 24 h. Severe AEs will be defined according to the International Conference on Harmonization guidelines [41]; any adverse event will be regarded as serious if it results in death, is life-threatening, requires hospitalization or prolongation of existing hospitalization, or results in persistent or significant disability or incapacity.

To assess safety, we will perform the following tests on participants at the screening phase (baseline) and on day 5 (the end of the intervention): routine blood, routine feces, routine urine, liver, and kidney function, and electrocardiography. Safety will be assessed according to the National Cancer Institute Common Terminology Criteria for Adverse Events, version 4.0.

In particular, we will pay attention to adverse drug reactions (ADRs) associated with SMI. Because of its effectiveness, the scope of diseases treated with SMI has gradually broadened, and reports of associated adverse reactions have increased correspondingly. The number of published literatures has ranked SMI ninth for ADRs in 33 varieties of Traditional Chinese Medicine injections in the 2004 edition of the National Essential Drugs List (2004 edition) in China [42].

Current evidence shows that SMI has a lower rate of ADRs. However, a systematic review of ADRs associated with SMI since 1995 showed that ADR cases were mainly systemic reactions (allergic shock), skin lesions (urticaria and pruritus), and local pain [43]. Because most ADRs occurred in the first 30 min of the first SMI administration, we suggest that patients should be closely observed during this period. Meanwhile, for patients who had continuous treatment with SMI, there is a need for close attention. ADR severity for each event as classified according to World Health Organization guidelines is shown in Table 1 [44].

**Table 1 Tab1:** Classification of adverse drug reaction (ADR) severity for Shenmai injection

Classification of ADR severity	
Class I	ADRs are deadly or life-threatening; patients need to be withdrawn from drugs and treated immediately; or ADRs last for more than 1 month.
Class II	Patients have pathologic and physiologic changes and must be withdrawn from drugs and treated; or ADRs last for more than 7 days.
Class III	Patients cannot endure the ADRs and must be given a lower dose or withdrawn from drugs; patients improve after symptomatic treatment.
Class IV	Patients can endure the ADRs, and no lowering of dose or drug withdrawal is necessary. Whether without treatment or through symptomatic treatment, patients improve

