#### Control group

Patients in the control group will receive only conventional therapy according to national guidelines.

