### Statistical analysis

Efficacy and safety analyses will be conducted according to the intention-to-treat principle. All statistical analyses will be performed using Statistical Packages of Social Sciences software (SPSS; version 19.0). All results made in this study are based on two-sided tests. A *P* value < 0.05 will be considered statistically significant. Continuous data will be presented as means and standard deviations and compared using the independent *t* test or Wilcoxon’s rank sum test, while categorical data will be presented as percentages or frequencies and compared using the chi-square or Fisher’s exact test. Data for subjects who meet the dropout criteria (i.e., incidence of serious AEs, < 80% compliance with the protocol, incomplete data that could influence the trial, reluctance to continue the study, large error in protocol, or deviation from the protocol) will be excluded. Missing values will be implemented by multiple imputations.

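### Added attention to adverse reactions is described for SMI patients only, so all-cause AEs may be recorded more completely in that arm; the size is unknown, and the remedy is to ask both arms in the same way (minor)

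*Protocol article*

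**What the plan says.** **Common to both arms (Safety).** An AE is any undesirable experience, "regardless of whether or not it is associated with the intervention". Capture is described for all participants: "Participants will be instructed to report AEs to the research team, and a research nurse will monitor participants for potential occurrences of AEs". Grading by CTCAE version 4.0 and the safety tests at baseline and day 5 (blood, feces, urine, liver, kidney, ECG) also apply to everyone.

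**Added for SMI only (Safety).** "In particular, we will pay attention to adverse drug reactions (ADRs) associated with SMI". For the first 30 minutes of the first dose, "we suggest that patients should be closely observed during this period". After that, "for patients who had continuous treatment with SMI, there is a need for close attention". No procedure, duration or recording rule is attached to this last statement.

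**Contact and blinding.** The SMI arm has an infusion once daily for 5 days (Intervention group). "Patients in the control group will receive only conventional therapy according to national guidelines" (Control group), with no sham or placebo infusion described. Patients and treating personnel are not blinded (Randomization, allocation concealment, and blinding).

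**Analysis (Statistical analysis).** The section covers both efficacy and safety. Its one rule for categorical data is that "categorical data will be presented as percentages or frequencies and compared using the chi-square" or Fisher's exact test, two-sided at 0.05. AEs are not named in that sentence. Nothing says whether events found only through the extra SMI attention enter the between-arm comparison.

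**The concern.** The AE definition is independent of cause and the patients are on chemotherapy, so many recorded events will be background symptoms such as nausea, itching or pain. Whether such symptoms reach the case report form depends on who asks, how often, and what they are looking for. If staff who know the allocation see SMI patients at an infusion every day and have been told to watch them closely, the same symptom can be more likely to be recorded in that arm.

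Safety is a stated aim of the trial. If the general categorical rule is applied to AE frequencies, the comparison mixes any drug effect with any detection effect. An excess on SMI could be a false alarm, and a true signal could be explained away as closer watching. How an event came to light cannot be reliably reconstructed after data collection, so this has to be settled in how the data are recorded.

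**Working it through.** **Plan's own figure.** The article gives no AE rate, no detection rate and no power for safety, so there is nothing of its own to reproduce here. The inputs taken from it are 47 patients per arm (Sample size estimation), the two-sided 0.05 level, and the two permitted tests (Statistical analysis).

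**Method.** Let the true AE risk be *p* in both arms, with capture probabilities c₁ (SMI) and c₀ (control). The recorded risks are then p·c₁ and p·c₀, and the relative detection is s = c₀/c₁. The false-positive rate is the sum of Bin(a; 47, p·c₁) × Bin(b; 47, p·c₀) over all pairs (a, b) for which the test gives P < 0.05. It was enumerated exactly for Fisher's test and for the chi-square test without continuity correction. All values of p, c₁ and c₀ are assumptions.

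**Step 1: the 30-minute window alone.** Five days are 5 × 24 = 120 hours, and 0.5/120 = 0.4%. If background events are spread evenly and the window adds complete capture only there, s is about 0.996. At a recorded SMI risk of 30%, the false-positive rate is 3.1% (Fisher) and 5.1% (chi-square), the same to one decimal as with s = 1.

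**Step 2: wider differences in capture.**

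| Assumed true risk | Assumed capture, SMI v control | s | Recorded risks | Fisher | Chi-square |
|---|---|---|---|---|---|
| 40% | 90% v 90% | 1 | 36% v 36% | 3.0% | 4.9% |
| 40% | 90% v 70% | 0.78 | 36% v 28% | 9.3% | 13.3% |
| 40% | 95% v 60% | 0.63 | 38% v 24% | 24.5% | 31.5% |
| 60% | 90% v 70% | 0.78 | 54% v 42% | 15.7% | 21.3% |

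In the unequal rows nearly all rejections show more events on SMI (in the second row, 13.1 of the 13.3 percentage points for chi-square).

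**Step 3: where it starts to matter.** Here SMI capture is taken as complete.

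| Recorded SMI risk | s | Fisher | Chi-square |
|---|---|---|---|
| 30% | 0.95 | 3.3% | 5.4% |
| 30% | 0.9 | 3.9% | 6.3% |
| 30% | 0.8 | 6.6% | 10.0% |
| 50% | 0.8 | 11.5% | 16.1% |
| 10% | 0.8 | 2.1% | 7.4% |

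The error stays near nominal down to about s = 0.9 at a 30% risk. It roughly doubles at s = 0.8 and rises further for more common events. For uncommon events it moves little, and Fisher's test stays below 5%. With 38 per arm instead of 47, the rates at 30% and s = 0.8 are slightly lower: 5.8% and 9.2%.

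**The case against.** The strongest reply is that the core of AE capture is the same in both arms: one definition, one instruction to self-report, one research nurse, one grading system and one set of tests. All patients come from an oncology inpatient department, so controls are also under ward care. Lower capture in controls is a possibility that the article does not demonstrate. This stands, and it is why the size must be left open.

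The sentence about close observation is a suggestion limited to the first 30 minutes of the first infusion. Acute reactions seen then would mostly be real effects of SMI, not artefacts of watching. This also stands. What remains is the open-ended attention during continued treatment, the daily infusion contact and the lack of blinding.

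A reader might infer that the plan commits to testing every AE between arms, including the reactions graded in Table 1. The text does not go that far. The categorical rule is general and does not name AEs, and Table 1 is a severity classification for SMI that can naturally be read as descriptive for that arm. AE tabulation and checklist schedules are also details that an article commonly leaves to the full protocol or SAP. The narrower point survives: the article itself states asymmetric attention and a general between-arm test, and does not say how the two fit together.

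Finally, unequal detection is common to open-label add-on trials. That is true, but here part of it can be reduced at little cost.

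**Conclusion.** The concern holds in limited form. The article describes added attention to SMI patients only, in an open-label trial with unequal contact, and its general rule would compare AE frequencies between arms. Subjective, all-cause events may therefore be recorded more completely on SMI.

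The size cannot be derived from the documents. It is negligible for the 30-minute window alone and becomes material only if control detection falls to about 0.8 or less of SMI detection for common events. In the mildest unequal case at a 40% true risk, the false-positive rate is about 9% to 13%, against 3% to 5% with equal capture. Both the capture rates and the true risks are assumptions.

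A reader might conclude that the extra observation will by itself produce a significant excess of events on SMI. The documents do not support that: the main ascertainment is shared, and in that same case 87% to 91% of trials would still show no significant difference. Severity: minor.

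**What to change.** Leave the observation of SMI patients as it is. Add the following to the Safety and Statistical analysis sections:

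- The research nurse asks about AEs with the same checklist and on the same schedule in both arms.
- The case report form records how each event was detected (checklist, spontaneous report, infusion observation, or scheduled test).
- The main between-arm comparison of all-cause AEs includes all events, whatever their source.
- A sensitivity comparison is limited to events from the common checklist and the baseline and day-5 tests.
- SMI-attributed reactions (Table 1 classes) are reported descriptively within the SMI arm.

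All events should stay in the main comparison because leaving out reactions seen only during infusion could understate real harm. The sensitivity comparison then shows whether an excess persists when both arms are asked alike. The checklist does not remove expectation effects, since patients and personnel remain unblinded.

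The cost is a little more time for a nurse who already monitors participants, one extra case report form field, and a few sentences of text.

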### Sample size estimation

The primary endpoint is the fatigue severity self-assessed using the FACIT-F subscale. The sample size is calculated based on the primary endpoint. Previous clinical practice suggests a mean difference (MD) of 4.95 between groups, and the same standard deviation (SD) of 7.28 for each group. Using a superiority test, it is estimated that 38 participants per group are needed to achieve 90% power and a (two-sided) 5% significance level in detecting treatment differences. Thus, the final sample size has been set at a total of 94 patients (47 in each group), assuming a 20% dropout rate.

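### On the stated inputs, 38 patients per group give about 83% power at two-sided 5%, not 90%; 38 matches a one-sided 5% test

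*Protocol article*

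**What the plan says.** The Sample size estimation section of the protocol article sizes the trial on its primary endpoint: "The primary endpoint is the fatigue severity self-assessed using the FACIT-F subscale". It gives these inputs:

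- effect: "Previous clinical practice suggests a mean difference (MD) of 4.95 between groups";
- spread: "the same standard deviation (SD) of 7.28 for each group";
- type of test: "Using a superiority test", with no margin given.

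It then states that "it is estimated that 38 participants per group are needed to achieve 90% power and a (two-sided) 5% significance level". The step to the recruitment target reads: "Thus, the final sample size has been set at a total of 94 patients (47 in each group), assuming a 20% dropout rate".

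The Statistical analysis section agrees on sidedness: "All results made in this study are based on two-sided tests", with significance at P < 0.05. For continuous data it names the independent t test or Wilcoxon's rank sum test. Allocation is 1:1 (section on randomization, allocation concealment, and blinding).

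**The concern.** Everything needed to recompute the sample size is printed, and 38 is too small for those inputs. It is the number that a one-sided 5% test would need, yet both the sizing and the analysis sections say two-sided. The test to be run is therefore stricter than the one the number 38 fits.

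The stake is the primary endpoint's power claim. A reader of a non-significant result would credit the trial with a 10% risk of missing a 4.95-point difference, when on the plan's own assumptions the risk is nearer 17%. An unresolved mismatch also leaves room for someone to settle it later, with data in hand, by moving to a one-sided test.

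**Working it through.** **Inputs** (Sample size estimation unless noted): difference 4.95; SD 7.28 in each group; alpha 0.05 two-sided; power 0.90; dropout 20%; 47 randomised per group. Allocation is 1:1 (randomization section). The margin is taken as 0 because none is stated.

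Standardised effect: d = 4.95 / 7.28 = 0.680, so d² = 0.4623.

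**1. Trying to reproduce 38 as stated.** Normal approximation, n per group = 2(z_α + z_β)² / d²:

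- Two-sided 5%, 90% power: 2(1.960 + 1.282)² / 0.4623 = 45.45, so 46. The exact noncentral-t calculation gives 47.
- The stated 38 is not reproduced.

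**2. Variants.**

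| Alpha | Power | n per group, normal | n per group, t |
|---|---|---|---|
| two-sided 5% | 80% | 34 | 35 |
| two-sided 5% | 85% | 39 | 40 |
| two-sided 5% | 90% | 46 | 47 |
| one-sided 5% | 80% | 27 | 28 |
| one-sided 5% | 85% | 32 | 32 |
| one-sided 5% | 90% | **38** | **38** |

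For the last row the unrounded normal value is 2(1.645 + 1.282)² / 0.4623 = 37.05, which rounds up to 38. Sizing for the rank sum test (dividing by its asymptotic efficiency of 0.955 under normality) only raises the number: 46/0.955 = 48.2 and 47/0.955 = 49.2 two-sided, 38/0.955 = 39.8 one-sided.

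Rounding of the inputs does not explain the gap. With the difference anywhere from 4.945 to 4.955 and the SD from 7.275 to 7.285, the two-sided requirement stays at 47.

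**3. Power actually delivered at two-sided 5%.** Noncentrality = 4.95 / (7.28 × √(2/n)), with 2n − 2 degrees of freedom:

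| Evaluable per group | Noncentrality | Power (t) |
|---|---|---|
| 37.6 (= 47 × 0.8) | 2.948 | 82.9% |
| 38 | 2.964 | 83.3% (84.2% normal) |
| 46 | 3.261 | 89.7% |
| 47 (no loss) | 3.296 | 90.3% |

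With a one-sided 5% test, 38 per group gives 90.2% (t) or 90.6% (normal).

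**4. Difference detectable with 90% power, two-sided 5%, SD 7.28.** 5.49 points at 38 per group and 5.52 at 37.6, so about 5.5.

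**5. Number to randomise for the stated design.** 47 / 0.8 = 58.75, so 59 per group, or 118 in total (46 / 0.8 = 57.5, so 58 per group and 116, by the normal approximation). The plan has 94, a gap of 24 (or 22).

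**The case against.** Four points can be made for the plan.

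*The trial randomises 47 per group, and 47 gives 90%.* True, but only if nobody is lost. The section presents 38 as the number needed and 47 as that number enlarged for 20% dropout, so the power claim is tied to 38. The Statistical analysis section declares intention-to-treat and multiple imputation, but also excludes patients who meet its dropout criteria. Some of those criteria, such as a serious adverse event or low compliance, need not mean a missing day-5 score. If such patients are kept, between 37.6 and 47 per group would be evaluable and power would lie between about 83% and 90%. So 83% is the power at the planned loss, not a fixed property of the trial. Imputation does not restore the information in outcomes that were never observed.

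*The one-sided explanation is an inference.* This stands: the article never mentions a one-sided test. A misprinted input would also fit, since 38 per group gives 90% two-sided power with an SD of about 6.57 or a difference of about 5.5. The one-sided match is exact and the simplest reading, but the inputs should be confirmed before the paragraph is rewritten.

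*An adjusted analysis could recover the power.* None is described; only unadjusted two-group tests are named.

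*The damage is moderate.* The final test remains two-sided at 5%, so type I error and the validity of the estimate are untouched. That limits the consequence but does not make the power statement true.

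**Conclusion.** The statement is wrong as written. With a difference of 4.95, an SD of 7.28 and a two-sided 5% t test, 38 per group gives 83.3% power, and 90% needs 47 evaluable per group. At the planned 20% loss from 47 per group, power is 82.9%, so the type II error is about 17% instead of 10%.

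This rests on the printed inputs being the intended ones, a superiority margin of zero and an unadjusted two-group comparison, which is all the article describes. The error does not depend on how 38 was obtained.

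A side remark carries no weight in this conclusion: 38 / 0.8 = 47.5 would round up to 48, not 47, which changes power by about 0.4 percentage points at 20% loss.

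**What to change.** First check the original calculation for the difference, the SD and the alpha that were entered. If 4.95 and 7.28 are confirmed, keep 94 patients and replace the power statement with wording to this effect:

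> With 94 patients (47 per group) and 20% dropout, the trial has about 83% power at a two-sided 5% level to detect a mean difference of 4.95 (SD 7.28), or 90% power to detect a difference of about 5.5.

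Add a sentence confirming that the primary test stays two-sided at 5%, and make both changes before any outcome comparison is seen. If an input proves to be misprinted, correct it and recompute the sentence.

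The cost is one paragraph and a less favourable stated power, with no extra patients. Keeping the stated 90% under the stated assumptions would instead take about 118 patients.

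A baseline-adjusted primary analysis could recover some power without recruiting more. If 7.28 is the SD of the day-5 score, which the article does not say, 37.6 per group reaches about 90% once the correlation between baseline and day 5 is about 0.44: the residual SD is 7.28 × √(1 − 0.44²) = 6.54, against about 6.53 needed. The article gives no such correlation, so this should not enter the power statement without data to support it.

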### Randomization, allocation concealment, and blinding

Patients who provide informed consent will be randomized into either a treatment group receiving a 5-day SMI regimen plus conventional therapy or a control group receiving only the conventional therapy. A block randomization sequence will be generated by SAS 9.2 (SAS Institute Inc., Cary, NC, USA) in a 1:1 ratio. Treatment assignments will be conducted using a web-based allocation system. Given the nature of the intervention, it is impossible to blind the patients and personnel involved in conducting the programs. Outcome assessors, laboratory technicians, data managers, and statisticians will be unaware of the treatment allocations.

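### Sample size: the stated 38 evaluable per group, 20% dropout and 47 enrolled per group do not quite agree, and the restated sentence must also carry the right power

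*Protocol article*

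**What the plan says.** All the figures stand in the protocol article, Sample size estimation. The planning values are given as "Previous clinical practice suggests a mean difference (MD) of 4.95 between groups" and "the same standard deviation (SD) of 7.28 for each group". From these, "it is estimated that 38 participants per group are needed to achieve 90% power" at "a (two-sided) 5% significance level in detecting treatment differences". The section then concludes that "the final sample size has been set at a total of 94 patients (47 in each group), assuming a 20% dropout rate", and it words this as a consequence of the 38. It shows neither the inflation formula nor a rounding rule.

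Two other sections bear on the check. Randomization, allocation concealment, and blinding fixes equal allocation. Statistical analysis confirms the sidedness: "All results made in this study are based on two-sided tests". That section also says that data from subjects who meet the dropout criteria are excluded, although it invokes intention-to-treat and multiple imputation as well.

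**The concern.** A reader who takes the 38, removes 20% and works forward does not arrive at 47. One who starts from 47 and removes 20% does not get back to 38. If dropout is exactly as assumed, the expected number analysed falls slightly below the number that the power statement rests on.

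This matters most if dropouts are left out of the analysis, which is one reading of the Statistical analysis section. In that case the 20% comes straight off the analysed sample. What is at stake is the internal consistency of the sample size statement and the power that may be quoted for it. The validity of the trial is not in question.

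**Working it through.** **Inputs** (protocol article, Sample size estimation, unless noted): mean difference 4.95; SD 7.28 in each group; power 90%; two-sided 5% (confirmed in Statistical analysis); 1:1 allocation (Randomization section); stated need 38 per group; dropout 20%; enrolment 47 per group, 94 in total. The standardised difference is 4.95/7.28 = 0.680.

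**Step 1. Reproduce the 38.** By the normal approximation, n per group = 2 × (SD × (z_alpha + z_power)/MD)².
- Two-sided 5%: 2 × (7.28 × (1.960 + 1.282)/4.95)² = 45.45, rounded up to 46. The exact t test needs 47.
- One-sided 5%: 2 × (7.28 × (1.645 + 1.282)/4.95)² = 37.05, rounded up to 38.

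The stated 38 is reproduced only with a one-sided 5% level, while the plan states two-sided.

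**Step 2. Inflate for dropout.** Enrolled = evaluable/(1 − dropout).
- From the stated 38: 38/0.8 = 47.5. The stated 47 is below this.
- Multiplying instead: 38 × 1.2 = 45.6, rounded up to 46. This does not give 47 either.
- From the unrounded one-sided figure: 37.05/0.8 = 46.3, rounded up to 47. This matches the stated enrolment.

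**Step 3. Work back from the enrolment.**
- 47 × 0.8 = 37.6 per group, a shortfall of 0.4 against 38.
- 94 × 0.8 = 75.2 in total against 76, a shortfall of 0.8.
- Dropout that 94 patients can absorb while keeping 38 per group: 1 − 38/47 = 19.1%.

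**Step 4. Power at the plan's two-sided 5% level** (MD 4.95, SD 7.28).

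| Evaluable per group | Normal approximation | Exact t test |
|---|---|---|
| 37 | 83.3% | 82.3% |
| 37.6 | 83.9% | 82.9% |
| 38 | 84.2% | 83.3% |
| 46 | 90.3% | 89.7% |
| 47 | 90.9% | 90.4% |

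By exact t test, the step from 38 to 37.6 costs 83.3 − 82.9 = 0.4 points. The gap between the stated 90% and the roughly 83% at 38 is about 7 points. It comes from Step 1, not from the dropout allowance. With 47 enrolled per group, two-sided power reaches 90% only if nobody is lost.

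**The case against.** The strongest defence is that 47 may be correctly derived. Inflating before rounding is a legitimate order, and 37.05/0.8 = 46.3 rounds up to 47. On that basis the expected 37.6 exceeds the 37.05 required, and one-sided power by the normal approximation is 90.4%. A reader might infer that the authors rounded 47.5 down. The article does not support that inference, because it shows no inflation step and this other route leads to exactly 47.

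The defence explains where 47 may have come from, but it does not make the printed figures agree. The article states 38 and never 37.05, and 37.05 rests on a one-sided level that the plan does not use.

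A second objection is that 20% is a planning guess, that 19.1% is about 20%, and that 0.4 patient lies well inside the uncertainty. This stands as a judgement of size, and it is why the point is minor. It also rules out another tempting argument, that 47 per group is unlikely to leave at least 38 in both groups. Inflating by an expected dropout rate is not meant to guarantee the target in each group, so that argument shows no error in the plan.

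A third objection is that the real problem lies in the 38 itself. That is correct, and it decides the form of the fix.

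**Conclusion.** The point holds as a small inconsistency. The stated need, dropout rate and enrolment do not agree: 38 evaluable at 20% dropout needs 47.5 enrolled per group, and 47 leaves 37.6. Ninety-four patients cover 19.1% dropout. The cost is 0.4 expected patient per group and about 0.4 points of power, and on its own it changes no decision about conduct, analysis or interpretation. Its cause is not documented.

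A reader might conclude that enrolling 48 per group (96 in total) would put the plan right. It would not. That leaves 48 × 0.8 = 38.4 evaluable per group, and the table gives only about 83% two-sided power by t test at 38, so the 90% claim would still be wrong. Changing only the dropout figure to 19% would leave the same claim standing.

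The conclusion assumes equal dropout in the two groups, analysis of about the number who remain, the stated MD and SD, and a t test. The rank-sum alternative and any covariate adjustment were not modelled.

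**What to change.** Keep 94 patients and rewrite the one sentence in Sample size estimation in either of these ways:

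- 94 patients (47 per group) allow for about 19% dropout if 38 per group are to remain; or
- 94 patients leave about 37 to 38 evaluable per group at 20% dropout.

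Whichever is chosen, the same sentence should quote the power at the two-sided 5% level for MD 4.95 and SD 7.28, about 82 to 83% by t test, in place of 90%. The edit is best made together with the correction of the one-sided/two-sided mismatch behind the 38, since that correction reworks the same figures.

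The cost is one sentence and a less favourable power figure. No extra patients are proposed, and neither the design nor the analysis changes.
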